#### Neuropathic pain intensity

The highest, average, and lowest neuropathic pain intensity ratings perceived in the prior week will be recorded using the 0–10 Numerical Pain Rating Scale with 0 being no pain and 10 being the worst pain ever [22]. This scale has been recommended by the mission of the Initiative on Methods, Measurement, and Pain Assessment in Clinical Trials consensus group for use in pain clinical trials and by the 2006 National Institute on Disability and Rehabilitation Research SCI Pain outcome measures consensus group [33, 34].

#### Location and impact of neuropathic pain: spasms frequency and severity

Other pain data will be collected using the National Institute of Neurological Disorders-Common Data Elements International SCI Pain Basic Data Set Version 2.0 [35]. This Data Set also assesses dimensions of pain (i.e., the intensity of pain, location, etc.), and how pain interferes with mood, activity, and sleep. The Brief Pain Inventory elicits self-report of pain intensity and its impact on functioning in the past 24 h [34]. Spasms frequency and spasm severity will be evaluated with the Penn Spasm Frequency Scale [36].

#### Mood

The Patient Health Questionnaire-9 assesses symptoms of depression [37–41]. The State-Trait Anxiety Inventory assesses current symptoms of anxiety (State anxiety) and a generalized propensity to be anxious (Trait anxiety) [42].

#### Quality of life

The World Health Organization Quality of Life Instruments (abbreviated version) assesses physical and psychological health, social relationships, and environment [43–45]. The Satisfaction with Life Scale assesses a person’s happiness with the current quality of life [46]. The Moorong Self-Efficacy Scale assesses self-efficacy related to everyday life activities in adults with SCI [47–49]. The Pittsburgh Sleep Quality Index assesses sleep quality [50].

#### Body awareness

The Revised Body Awareness Rating Questionnaire assesses how pain or tension in the body is affecting participants’ awareness and function in daily life (e.g., being comfortable when lying down) [51]. The Postural Awareness Scale measures awareness of body posture in patients with chronic pain [52]. The Functional Appreciation Scale measures the level of appreciation one has for the functionality of the body [53]. The Multidimensional Assessment of Interoceptive Awareness measures interoceptive body awareness [54]. The Body perception questionnaire-short form measures interoceptive awareness and autonomic reactivity [55, 56]. Participants self-report whether their cardiopulmonary system, bladder, bowel, and sexual function are normal or abnormal with the Autonomic Standards Assessment Form [57].

#### Function

The Spinal Cord Injury Functional Index [58] measures functional performance across five domains: basic mobility, self-care, fine motor function, wheelchair mobility, and/or ambulation [59]. For the Patient Specific Functional Scale [60], the participants will self-identify goals related to activities in daily life that are important to them. The participants will rate them at each time point between 0 (i.e., unable to do the activity without pain) and 10 (able to do the activity without pain) [60]. For the Physical activity 3-day recall questionnaire, the participants describe all activities performed during the past 3 days [61, 62].

#### Fear of injury due to movement

The Tampa Scale for Kinesiophobia assesses fear of injury due to physical movement [63].

#### Community integration

The Craig Handicap Assessment and Reporting Technique–Short Form is used to assess community integration [64].

### Participant timeline

Table 1 displays the scheduling of assessments and timeline of each study section.

**Table 1 Tab1:** Scheduling of enrolment, intervention, and assessments

	Study period				
	Enrolment + Baseline assessment	Intervention + assessments		6-week Follow-up period (no intervention)	1-year Follow-up period (practice at will) + close-out
Timepoint	*Week 0*	*Week 6*	*Week 12*	*Week 18*	*1-year*
Enrolment:					
Eligibility screen	X				
eConsent	X				
Intervention:					
*Qigong practice for 12 weeks, at least 3* × */week*		X	X		X
Assessments:					
*Demographic and general health data*	X				
Weekly assessment of the highest, average, and lowest neuropathic pain intensity levels in the prior week	X	X (weekly)	X (weekly)	X (weekly)	X
* Other outcome assessments*	X	X	X	X	X

### Data collection and management

#### Plans for assessment and collection of outcomes

The study staff member will acquire demographic information and general health history and screen participants for cognitive ability with the Mini-Mental State Examination-short version [65], and for kinesthetic imagery with the Kinesthetic and Visual Imagery questionnaire [66]. All data in this study will be entered into the REDCap database.

#### Plans to promote participant retention and complete follow-up

Participants will be encouraged to complete all scheduled virtual visits and assessments. Given that this study is starting during the COVID-19 pandemic, we estimate 90% adherence and 30% attrition given a high likelihood of some participants being exposed to COVID-19 during the study. If an assessment or weekly check-in is missed, care will be taken to get the information at a later time. There are no stop criteria for missed sessions or testing. The study team will decide when to consider a participant “lost to follow-up” based on clinical/scientific judgment on a case-by-case basis. Missed testing sessions will be recorded for consideration during the analysis but will not be cause for removal from the study.

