**Table Taba:** 

Feasibility item and details	Benchmark
*Recruitment/enrollment* ◦ Assess recruitment rates (screens and enrollment, sex/racial outcomes) ◦ Evaluate the recruitment rate for complete and incomplete SCI	◦ The proportion of potential participants contacted who agreed to participate: 80% is excellent and 70% good ◦ Ratio of complete/incomplete SCI. We estimate recruitment of 30–40% of adults with complete, 60–70% with incomplete SCI ◦ Reasons for (not) participating will help delineate facilitators and barriers to participation
*Feasibility and acceptability of the study design* ◦ Drop-out rates	◦ Proportion of people withdrawing from the study and the reason for withdrawing. A proportion of 90% staying in the study is excellent, 80% good (i.e., 20% drop-out)
*Feasibility, adherence, and acceptability of the Qigong practice* ◦ Assess intervention adherence, average Qigong practice; at least 3×/week (123 min)	◦ Weekly/monthly check-ins (reporting min/week of practice) to monitor adherence. The Spring Forest Qigong^TM ^website also logs the day, time, and duration of video access ◦ Feasibility: Excellent: > 80% participants practice at least 2 × /week; good ≥ 70% ◦ Drop-out due to lack of interest will be counted as general attrition: 10% drop-out is excellent, 20% is good
*Feasibility of adhering to the collection of quantitative measures* ◦ % Adherence in completing all assessments during the study (until 6 weeks follow-up) ◦ % adherence for the 1-year post-intervention assessments	◦ Feasibility is ‘excellent’ when none of the questionnaires are fully missing in > 25% of the participants
*Program satisfaction* ◦ interview about satisfaction with the Qigong practice, and the study	◦ Excellent satisfaction: ≥ 75% of participants report being satisfied with the study and Qigong practice; and good if ≥ 70% of participants are satisfied. We will ask them about satisfaction at the end of the 12 weeks of practice and at the end of the 6-week, and 1-year follow-up
*Program safety* ◦ Assess adverse events (IRB + Good Clinical Practice reporting guidelines)	◦ Excellent safety: no study-related adverse events; good if there are minimal and mild adverse events (e.g., muscle soreness) linked to Qigong practice in max 10% of participants. We will ask about adverse events on our weekly and monthly check-in calls

We will collect patient-centered outcome measures on neuropathic pain intensity and symptoms associated with pain.

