### Statistical methods

#### Sample size

To our knowledge, this will be the first study evaluating the feasibility of Qigong on neuropathic pain perception. This study will also provide preliminary estimates of effect size, crucial to generate hypotheses for future larger randomized controlled trials. We will recruit a total sample size of 18 participants. This is based on our estimated accrual rates. With the sample size, we will be able to estimate the rate parameters of our feasibility endpoints between 70 and 90% to be within 95% confidence intervals of ± 21% and ± 14% respectively. Based on data from another body awareness therapy in adults with SCI [25], the sample size will also lead to 95% confidence intervals for pain estimates of ± 0.5.

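### Retention is graded against an 80% mark while 30% attrition is forecast, but loss to follow-up has no fixed definition and the pain precision assumes all 18 participants stay

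*Protocol article*

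**What the plan says.** **Forecast.** Under Plans to promote participant retention and complete follow-up: "we estimate 90% adherence and 30% attrition given a high likelihood of some participants being exposed to COVID-19". No time point is attached.

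**Benchmark.** The table under Feasibility benchmarks measures drop-out as "Proportion of people withdrawing from the study and the reason for withdrawing" and grades it: "A proportion of 90% staying in the study is excellent, 80% good (i.e., 20% drop-out". The row on adherence to Qigong repeats the limits: "Drop-out due to lack of interest will be counted as general attrition: 10% drop-out is excellent, 20% is good". Neither row says when drop-out is counted (week 12, week 18 or 1 year). Neither says whether COVID-19 exits or removals by the investigator are included.

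**Who is lost.** The retention section lets the study team decide when a participant is lost to follow-up, "based on clinical/scientific judgment on a case-by-case basis". It adds: "There are no stop criteria for missed sessions or testing". Missed assessments are to be sought later and do not lead to removal. Separately, Criteria for discontinuing or modifying allocated interventions lists grounds for removal, including a request to withdraw.

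**Sample size.** "We will recruit a total sample size of 18 participants", a number based on accrual. The section gives 95% half-widths of ±21 and ±14 points for feasibility rates of 70% and 90%, and ±0.5 for pain. It does not mention attrition.

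**The concern.** Feasibility is the main product of this pilot. Statistical methods says the estimates will help decide whether to proceed to a larger randomized trial, and the markers are described as set in advance. The plan expects to retain fewer people than its lowest named grade requires, so retention is likely to be read near or below the 80% line. There, the definition of the count matters most.

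That definition is loose for one group: participants who stop responding without asking to withdraw. They count against retention only if the team decides they are lost. With 18 participants, one such decision can change the grade, and it can be taken with the result in view.

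The same forecast bears on the pain estimates. They are meant to supply effect sizes for future trials, yet their quoted precision makes no allowance for losing 30% of the sample.

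**Working it through.** **Inputs.** n = 18 and the half-widths (±21 points, ±14 points, ±0.5) come from Sample size. Attrition of 30%, hence retention of 70%, comes from the retention section. The thresholds of 80% and 90% come from the feasibility table.

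**Step 1: the plan's own rate precision.** The Wald half-width is 1.96 × √(p(1−p)/n).
- p = 0.70: 1.96 × √(0.21/18) = 0.212
- p = 0.90: 1.96 × √(0.09/18) = 0.139

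These reproduce ±21% and ±14% with all 18 in the denominator.

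**Step 2: counts behind the grades.**
- 'Good': 0.80 × 18 = 14.4, so 15 must stay (15/18 = 83.3%; 14/18 = 77.8% falls short).
- 'Excellent': 0.90 × 18 = 16.2, so 17 must stay.
- Forecast: 0.70 × 18 = 12.6, so 12 to 13 stay.

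**Step 3: chance of reaching a grade on the forecast.** X is Binomial(18, 0.70), which treats participants as independent and assumes that forecast and benchmark cover the same period.
- P(X ≥ 15) = 0.1046 + 0.0458 + 0.0126 + 0.0016 = 0.165, about one in six
- P(X ≥ 17) = 0.0126 + 0.0016 = 0.014

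Sensitivity of the chance of 'good':

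| True retention | P(X ≥ 15) |
|---|---|
| 65% | 0.078 |
| 70% | 0.165 |
| 75% | 0.306 |
| 80% | 0.501 |

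If 14/18 were accepted as 80%, the chance at 70% retention would be 0.333.

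**Step 4: weight of one classification.** 1/18 = 5.6 points. Moving one person from lost to retained changes 14/18 (77.8%) to 15/18 (83.3%) and crosses the line. The exact 95% intervals are 52.4% to 93.6% and 58.6% to 96.4%. They overlap almost entirely, so it is the grade that is fragile, while the interval moves only modestly.

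**Step 5: pain precision.** The standard deviation behind ±0.5 is not given, so the figure cannot be reproduced directly. It can be rescaled.

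Square-root scaling, 0.5 × √(18/m):
- m = 13: 0.5 × 1.177 = 0.59
- m = 12: 0.5 × 1.225 = 0.61

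With t quantiles (2.110 for 17 degrees of freedom, 2.179 for 12, 2.201 for 11), ±0.5 at n = 18 implies a standard deviation of 0.5 × √18 / 2.110 = 1.005.
- m = 13: 2.179 × 1.005 / √13 = 0.61
- m = 12: 2.201 × 1.005 / √12 = 0.64

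Either way the half-width is about ±0.6.

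**The case against.** The strongest reply is that nothing here is an error. A forecast is a planning guess and a benchmark is a quality standard. Lowering the standard to match a pessimistic guess would be worse practice. This stands, and the thresholds should remain.

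Several stronger readings are tempting, but the document does not support them:

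- **That the trial is set up to be declared not feasible.** The table names only 'excellent' and 'good'. It has no failing grade and no go/no-go rule. Rates are to be reported with exact intervals, and reasons for withdrawal are collected, so pandemic exits can be identified.
- **That drop-out as a whole is a matter of judgment.** Only lost-to-follow-up status is left to case-by-case decision. Withdrawal on request is objective. Among the other removal grounds, intercurrent illness also rests on the principal investigator's judgment.
- **That 30% attrition breaches the data-collection benchmark.** That benchmark asks that "none of the questionnaires are fully missing in" more than 25% of participants, which is 5 or more of 18. A person who leaves after baseline has already completed the baseline questionnaires. A breach follows only on a per-visit reading that the table does not state.
- **That the benchmarks disagree.** Four losses of 18 (22%) may be graded differently on retention and on questionnaire completeness, but these are different measures with different cut-offs.

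Two further replies have force. One-person sensitivity is inherent in 18 participants, and even true retention of 80% reaches 'good' only half the time. An operational rule for loss to follow-up is also often left to a fuller document. Here, however, the article does not leave the rule open: it states one, and that rule is discretionary. Finally, the plan intends multiple imputation and inverse probability weighting, which may use partial data. The ±0.6 therefore applies where post-baseline estimates rest on completers.

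**Conclusion.** The point holds as a clarification of modest weight; the plan does not contradict itself. Its forecast of 12 to 13 retained lies below the 15 needed for 'good', and the document does not comment on the gap. The chance of reaching 'good' is 0.165 if both figures cover the same period, true retention is 70% and participants are independent. If the 30% refers to the full year, that probability does not carry over to week 12 or week 18.

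Two consequences follow. The retention marker lacks a time point and a fixed rule for silent non-responders, so one classification worth 5.6 points can change its grade. The ±0.5 for pain is optimistic on the plan's own forecast and becomes about ±0.6 (0.59 to 0.64 across the two methods) for completers. The feasibility-rate precision of ±21 and ±14 points is unaffected for retention, because its denominator is all 18.

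**What to change.** 1. Keep the 80% and 90% thresholds. For the retention marker, replace case-by-case judgment with a fixed count: not retained is every enrolled participant without the week-12 assessment and, separately, every enrolled participant without the week-18 assessment, for any reason, over all 18. Since missed assessments may be collected later, state by when a late one still counts.
2. In Sample size, restate the pain precision for 12 to 13 evaluable participants (about ±0.6) beside the figure for 18. Leave the feasibility-rate denominators at 18.
3. Optionally, tabulate COVID-19 exits separately, using the withdrawal reasons already collected.

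The cost is a wording amendment with ethics board review and, if item 3 is adopted, one small table. No new data or participants are needed, and clinical management does not change. The downside is that the retention and pain-precision figures may look slightly less favourable.

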#### Data management

Clinical and weekly check-in data will be entered into the REDCap database, which uses a MySQL database via a secure web interface. During the project, data will be accessible to collaborators through the secure REDCap system by username and password; users are given only the permissions they need to carry out their responsibilities. The MySQL database and the web server will both be housed on secure servers operated by the Academic Health Center’s Information Systems group (AHC-IS). Servers are in a physically secure location on campus and are backed up nightly, with the backups stored in accordance with the AHC-IS retention schedule of daily, weekly, and monthly tapes retained for 1 month, 3 months, and 6 months, respectively. Weekly backup tapes are stored offsite. The AHC-IS servers provide a stable, secure, well-maintained, and high-capacity data storage environment, and REDCap is a widely used, powerful, reliable, well-supported system.

The clinical data on REDCap will be verified and maintained by the study staff and the biostatistician. Source data will be verified for accuracy, and completeness by comparing the data to external data sources (for example, medical records). Data collection forms will all be numerically coded to ensure privacy and data integrity.

#### Confidentiality

Research records will be stored in a confidential manner to protect the confidentiality of information of the participants. Participant confidentiality will be safeguarded using password protected databases and locked file cabinets. Research records use the participant code only, with keys identifying individual participants available only to the PI or selected and approved designees. Records of the combined HIPAA-eConsent will be securely stored on the REDCap database server. Further, access to identifiable private information from study participants will only be accessible to study related personnel who have met the UMN’s training requirements for the Responsible Conduct of Research, Good Clinical Practice, HIPAA, and data security and have completed all initial and annual study specific training.

#### Plans for collection, laboratory evaluation and storage of biological specimens for genetic or molecular analysis in this trial/future use

Not applicable, since no such data will be collected in this study.

### Statistical methods

#### Sample size

To our knowledge, this will be the first study evaluating the feasibility of Qigong on neuropathic pain perception. This study will also provide preliminary estimates of effect size, crucial to generate hypotheses for future larger randomized controlled trials. We will recruit a total sample size of 18 participants. This is based on our estimated accrual rates. With the sample size, we will be able to estimate the rate parameters of our feasibility endpoints between 70 and 90% to be within 95% confidence intervals of ± 21% and ± 14% respectively. Based on data from another body awareness therapy in adults with SCI [25], the sample size will also lead to 95% confidence intervals for pain estimates of ± 0.5.

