#### Statistical methods

Rate parameters for the feasibility markers will be estimated based on the participants who achieved each benchmark, with 95% confidence intervals constructed based on exact binomial confidence interval. The continuous measures of feasibility will be summarized using descriptive statistics with 90% confidence intervals constructed. The occurrence of protocol deviation or non-adherence will be summarized and tabulated using frequency tables. The reasons of protocol deviation or non-adherence will be documented and investigated for improved clinical design in future large studies.

All quantitative variables will be summarized using descriptive statistics for all subjects as well as each group at each time point. For longitudinal outcomes, across-time changes and correlations will also be estimated for all participants as well as each group that will be used for sample size determination in future studies. All analyses will be done using standard statistical software including SAS, Stata, and R. The data analysis from this quasi-experimental study will provide an estimate of key trial elements to determine whether to proceed to a larger definitive randomized controlled trial.

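### The ±21% and ±14% precision figures are normal-approximation half-widths at n = 18; the planned exact binomial intervals reach further down, mainly near 90%

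*Protocol article*

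**What the plan says.** The Sample size section sets the size and its basis: "We will recruit a total sample size of 18 participants", followed by "This is based on our estimated accrual rates". It then describes what that number gives: "we will be able to estimate the rate parameters of our feasibility endpoints between 70 and 90% to be within 95% confidence intervals". The half-widths it states are ±21 points at a rate of 70% and ±14 points at 90%.

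The Statistical methods section fixes how the feasibility rates will be reported: "with 95% confidence intervals constructed based on exact binomial confidence interval".

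The section on retention and complete follow-up states the expected loss: "we estimate 90% adherence and 30% attrition given a high likelihood of some participants being exposed to COVID-19". The precision sentence mentions neither the exact method nor this attrition.

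**The concern.** A symmetric ± at a rate of 70% or 90% with 18 people points to a normal approximation. Exact binomial intervals at those rates are not symmetric, so no single ± describes them, and the longer arm is the lower one. The feasibility benchmarks for recruitment, retention, adherence and satisfaction are floors, so the lower limit is what a reader will look at.

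The article says its results will inform whether to go on to a larger randomized trial. Someone planning that trial, and taking ±14 at face value, would expect an observed rate near 90% to come with a lower limit of about 76%. The planned analysis will not deliver that. The figure also assumes that all 18 contribute to every rate, although the article itself expects 30% attrition.

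**Working it through.** **Inputs.** n = 18, rates of 70% and 90%, and 95% confidence (Sample size); exact binomial intervals (Statistical methods); 30% attrition (retention section).

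**1. Reproducing the stated figures.** The Wald half-width is 1.96 × √(p(1 − p)/n).

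- p = 0.70: 1.96 × √(0.70 × 0.30/18) = 0.2117, or 21%.
- p = 0.90: 1.96 × √(0.90 × 0.10/18) = 0.1386, or 14%.

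Both match. The alternatives tried do not give the pair 21/14 (half-widths in points at 70% / 90%):

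- exact at n = 18: 22.3 / 16.1
- Wilson at n = 18: 19.5 / 14.4
- 90% Wald at n = 18: 17.8 / 11.6
- Wald at n = 13: 24.9 / 16.3
- Wald at n = 12: 25.9 / 17.0

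**2. The planned method at n = 18.** For x successes in n, the exact (Clopper–Pearson) lower limit is the 2.5% quantile of Beta(x, n − x + 1). The upper limit is the 97.5% quantile of Beta(x + 1, n − x). The first two rows use non-integer x (12.6 and 16.2) to sit at exactly 70% and 90%; the last two are attainable counts.

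| Observed | Exact 95% CI | Lower / upper arm (points) | Mean half-width (points) |
|---|---|---|---|
| 70% | 44.3–88.9% | −25.7 / +18.9 | 22.3 |
| 90% | 66.7–99.0% | −23.3 / +9.0 | 16.1 |
| 13/18 (72.2%) | 46.5–90.3% | −25.7 / +18.1 | 21.9 |
| 16/18 (88.9%) | 65.3–98.6% | −23.6 / +9.7 | 16.7 |

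The stated ±14 implies a lower limit of 90 − 14 = 76%. The exact method puts it at 66.7% for a rate of exactly 90%, and at 65.3% for the nearest attainable count, 16/18.

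**3. Rates known only for those who remain.** If the 30% applies to the 18 enrolled, 18 × 0.7 = 12.6, so about 12 or 13 people.

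| Observed | Exact 95% CI | Lower / upper arm (points) |
|---|---|---|
| 9/13 (69.2%) | 38.6–90.9% | −30.7 / +21.7 |
| 12/13 (92.3%) | 64.0–99.8% | −28.3 / +7.5 |
| 9/12 (75.0%) | 42.8–94.5% | −32.2 / +19.5 |
| 11/12 (91.7%) | 61.5–99.8% | −30.2 / +8.1 |

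**The case against.** The strongest reply is that nothing will be mis-analysed. The reported intervals will be exact, as planned, and an approximate planning half-width beside an exact analysis is common in a pilot. The change in overall width from the method alone is small: 21.2 to 22.3 points at 70%, and 13.9 to 16.1 at 90%. This stands, and it limits the severity. It does not rescue the ±14, because the lower arm there is 23 to 24 points.

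Three stronger readings are tempting, and the documents do not support them.

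- *The sample size is unjustified.* The article bases 18 on accrual. The precision sentence describes what 18 yields and did not produce it. It is also one of two precision statements, the other being ±0.5 for pain.
- *Attrition widens every feasibility interval.* Retention is measured on everyone enrolled. Recruitment is measured on people contacted, of whom there are at least 18. Adherence is tracked by website logs and can be counted on all 18, with drop-outs as failures. Only rates that need an answer from those who remain, such as satisfaction and late assessments, fall to about 12–13. The article plans multiple imputation and inverse probability weighting for missing data, but neither restores the information of 18 observed answers.
- *A rate cannot be called good unless its lower limit clears 70%.* The feasibility table grades observed proportions, and its marks differ by item. For retention it reads "A proportion of 90% staying in the study is excellent, 80% good (i.e., 20% drop-out". No planned decision depends on a lower confidence limit.

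**Conclusion.** The point holds as a correction of a stated figure, moderate to minor in weight. The ±21% and ±14% do not come from the interval method the article commits to. The 70% figure is close in overall width but hides a lower arm of about 26 points. The 90% figure is materially off on the lower side: about 65–67% rather than the implied 76%.

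The n = 18 results rest only on the article's own inputs. The 12–13 figure assumes that 30% of the 18 enrolled are lost before the rate in question is measured. The article does not say when the losses are expected, so a satisfaction rate at 12 weeks could rest on anything from about 12 to 18 people.

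**What to change.** Replace the precision sentence for feasibility rates in the Sample size section with:

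> 'With 18 participants the exact 95% CI is about 47–90% for an observed 13/18 (72%) and 65–99% for an observed 16/18 (89%). For rates known only for participants who remain, such as satisfaction and late assessments, the 30% attrition expected in the protocol leaves about 12–13 people, and the exact 95% CI is then about 39–91% (9/13) and 64–100% (12/13).'

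Leave the sample size, the benchmarks and the exact method as they are. Do not add a rule that a true rate below 70% counts as excluded only at 17/18 or better. That would be a new criterion, and it does not carry over to other denominators: with 13 evaluable people, 13/13 would be needed (lower limit 75.3%; 12/13 gives 64.0%).

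The cost is a change of wording. The downside is that the stated precision looks less favourable.

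### The ±0.5 precision for pain needs complete data on all 18 recruits; after the plan's own 30% attrition it is about ±0.6

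*Protocol article*

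**What the plan says.** The Sample size section of the protocol article states: "We will recruit a total sample size of 18 participants". It gives the reason as: "This is based on our estimated accrual rates". No allowance for dropout is mentioned.

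Three precision figures are then attached to that number. For feasibility, "we will be able to estimate the rate parameters of our feasibility endpoints between 70 and 90" per cent, with 95% half-widths of ±21% and ±14% respectively. For pain, the section continues "Based on data from another body awareness therapy in adults with SCI" and concludes that "the sample size will also lead to 95% confidence intervals for pain estimates of" ±0.5. The SD behind this is not printed; the reader is referred to the earlier study.

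The pain measure is described under Neuropathic pain intensity: "The highest, average, and lowest neuropathic pain intensity ratings perceived in the prior week will be recorded", on a 0–10 "Numerical Pain Rating Scale with 0 being no pain and 10 being the worst pain ever".

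Under Plans to promote participant retention and complete follow-up, the article says "we estimate 90% adherence and 30% attrition", citing the pandemic. It ties the 30% to no particular visit. The section on missing data plans multiple imputation and inverse probability weighting.

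**The concern.** The Sample size section treats the number recruited as the number analysed, while the retention section expects to lose nearly a third of them. Nothing in the article reconciles the two. The estimates most exposed are those at the later time points, and these include the pre-post changes in pain that the Objectives ask about and that the Statistical methods section intends to use in sizing future studies. If the stated half-width holds only without dropout, the article promises a precision for those estimates that its own planning assumptions do not deliver.

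**Working it through.** **Inputs.** n = 18 recruited, 95% confidence and half-width 0.5 (Sample size); 30% attrition (retention section). The SD is not given and has to be solved for.

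**Step 1: which n lies behind the paragraph?** The figures for rates can be checked without an SD, using 1.96 × √(p(1 − p)/n):

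| n | p = 0.70 | p = 0.90 |
|---|---|---|
| 18 | 21.2% | 13.9% |
| 13 | 24.9% | 16.3% |
| 12 | 25.9% | 17.0% |

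The stated ±21% and ±14% match n = 18. The pain figure is attached to the same sample size, so it too is read as using all 18.

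**Step 2: the SD implied by ±0.5 at n = 18.** The half-width of a 95% interval for a mean is t(0.975, n − 1) × SD/√n, or 1.96 × SD/√n by the normal approximation. Solving for the SD:
- t: 0.5 × √18 / 2.110 = 1.01
- normal: 0.5 × √18 / 1.96 = 1.08

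So ±0.5 cannot be reproduced directly, but it is consistent with an SD of about 1.0 to 1.1.

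**Step 3: participants left after attrition.** 18 × (1 − 0.30) = 12.6, that is 12 to 13.

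**Step 4: half-width with the same implied SD.** The factor t(0.975, n − 1)/√n is 0.497 at n = 18, 0.604 at n = 13 and 0.635 at n = 12.

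| n | t, SD 1.01 | normal, SD 1.08 |
|---|---|---|
| 18 | 0.50 | 0.50 |
| 13 | 0.61 | 0.59 |
| 12 | 0.64 | 0.61 |

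The half-width is therefore 0.59 to 0.64, which is 18% (0.588/0.5) to 28% (0.639/0.5) wider than stated.

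**Step 5: sensitivity.**
- If ±0.5 is itself rounded from anywhere between 0.45 and 0.55, the implied SD is 0.90 to 1.19 and the half-width at 12 to 13 participants is 0.53 to 0.70.
- To keep ±0.5 with 12 to 13 participants, the SD would have to be 0.79 to 0.83 (t) or 0.88 to 0.92 (normal).
- At the retention that the feasibility table calls good (80%, about 14 participants) the half-width is 0.57 to 0.58; at the level it calls excellent (90%, about 16) it is 0.53 to 0.54.

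**The case against.** The best reply is that little depends on this figure. The sample size was set by accrual, pain precision is a by-product, there is no power claim, and a later trial would use the SD and change observed here and not this forecast. That is right, and it keeps the point minor.

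The loss is also not uniform. The 30% has no date attached, follow-up runs to one year, and pain is recorded weekly to the end of the 6-week follow-up, so those who leave late still contribute earlier ratings. Baseline has all 18. Missed assessments are to be obtained later where possible. So 12 to 13 is the count once attrition has run its course, not the number at every post-baseline week. Multiple imputation and weighting may also recover some information, though not the precision of 18 complete records.

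Rounding is a fair objection too. At the lower edge, a true half-width of 0.45 at n = 18 becomes 0.53 to 0.55 at n = 13 and could still be printed as ±0.5.

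A reader might go further and infer that the real interval is about ±1 or more. That needs an SD of 1.5 to 2.0, which the documents do not give; the earlier study is not at hand, and its SD may well be near 1.0. Nor does the entry criterion (a highest rating of at least 3) show that 1.0 is too small. It concerns the highest rating at entry, and says nothing about the SD of the average or lowest rating or of a change.

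**Conclusion.** The point stands as a modest overstatement of precision. The ±0.5 is a complete-data figure for 18 participants. Under the article's own 30% attrition, the half-width for later pain estimates is about ±0.6 at the implied SD, a difference of about 0.1 point on a 0–10 scale.

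This rests on three assumptions: that ±0.5 was calculated at n = 18, as the companion figures indicate; that it is a simple interval for a mean, so that the SD can be back-solved; and that the same SD applies after dropout.

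It would be tempting to conclude that a 1-point mean reduction could no longer be told from no change. The figures do not support that. At the implied SD with 12 participants, an estimate of 1.0 has an interval of about 0.36 to 1.64. Zero would be included only if the SD exceeded about 1.57 (1/0.635, n = 12) or 1.66 (1/0.604, n = 13). Nor is the absence of a printed SD or a named rating a defect in its own right, since a condensed article can leave both to the full protocol or the analysis plan.

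**What to change.** Reword the last sentence of the Sample size section on these lines: with complete data on 18 participants, as at baseline, the 95% interval for mean pain has a half-width of about 0.5; for estimates after the expected 30% attrition (12 to 13 participants) it is about 0.6. Insert the SD taken from the earlier study, say whether it is the SD of a level or of a change from baseline, and recalculate both half-widths from it if it differs from the implied 1.0 to 1.1. A cross-reference to the retention section would reconcile the two passages.

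The cost is wording only, with a slightly less favourable figure. No change to the sample size, design or analysis is needed. For reference, ending with 18 participants after 30% attrition would take 18/0.7 = 25.7, so 26 recruits, but since the sample size was set by accrual, restating the precision is the proportionate remedy.
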